**Figure 1 F1:**
[figure not shown]
**Diagram of Study Flow**.

Overall Eat Smart provides a treatment protocol for use at a tertiary centre to assist obese adolescents seeking weight loss advice to reduce their weight. The first phase will evaluate the relative efficacy of two supported and structured 12 week weight reduction diets and an untreated control group:

(i) reduced carbohydrate (35% carbohydrate, 30% protein, 35% fat)

(ii) reduced fat (55% carbohydrate, 20% protein, 25% fat)

(iii) control - offered the dietary group of their choice (i or ii) after a 12 week waiting period

The primary outcome variable is reduction of BMI z-score. Secondary outcome variables are reduction in body fat and alteration in metabolic profile after 12 weeks. The psychological diagnostic interviews will document the extent and nature of psychological health in obese adolescents. In the second phase, with follow-up to 24 weeks, the relative efficacy of the low fat versus the reduced carbohydrate diet on BMI z-score.

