### Hypotheses to be tested

#### After 12 weeks

• There will be a difference in change in BMI z-score between the intervention diets and the control group.

• There will be a difference in the change of mean BMI z-score between the low fat and the reduced carbohydrate group.

• There will be a difference in the change of % body fat, markers of inflammation, insulin resistance and in lipid profile between the reduced carbohydrate group and the low fat group.

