### Statistical Analysis Plan

Primary analysis will use the intention to treat principle, assuming return to baseline values for non-completers. Differences between participants who completed and withdrew will be assessed using t tests for continuous variables and Fisher's Exact Test for categorical variables. We shall examine weight loss over time using a mixed-effects model with a random intercept and slope for each participant. This method controls for the non-independence in results from the same participant and allows for heterogeneity between participants. Potential co-variates (gender, Tanner Stage, baseline weight) will be assessed, and, if appropriate, incorporated into the model. We will examine the effects of losses of body weight and body fat on clinically important markers of disease risk (lipids, blood pressure, waist: hip ratio, insulin resistance) using analysis of covariance. Data generated from the psychometric questionnaires (self-concept, anxiety, self-esteem and quality of life) will be used as secondary outcome variables to examine the extent and nature of psychological distress in obese adolescents pre-treatment and mixed-effects models will be used to examine changes in these parameters and their relationship with weight and waist: hip ratio change. Statistical significance will be based on two-tailed tests, with p < 0.05 considered significant.

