## Discussion

There is a lack of clinical studies which assess the effectiveness of specific treatment pathways for obese adolescents. In particular there is no information as to the effect of how alteration of the carbohydrate content of the diet will change body composition or metabolic parameters. This study protocol will contribute also to our understanding of body composition of obese adolescents and the effect of weight loss on different body compartment changes.

Our feasibility study suggested that tailored energy prescription and structured advice was the preferred option for treatment seeking adolescents and their families. In particular the need for information on how much to eat i.e. portion size was requested. If the reduction in dietary carbohydrate has no adverse effects on cardiovascular risk factors, the option to decrease carbohydrate would broaden the choice of dietary patterns based on preference of the adolescent and their family that could be offered in practice.

This study has a unique preparatory psychological preparatory phase and screening for psychological disturbance prior to randomisation which ensures that all subjects enter the study without any clinical levels of psychological diagnosis. The additional measurement of eating behaviours and other psychological parameters is designed to monitor any risk to psychological health associated with the intervention. The relatively short time frame allows biochemical parameters and psychological parameters to be measured before taking the study into a longer duration.

This study is designed to address the gap in the evidence base for optimal weight management interventions in obese adolescents in a clinical setting and to examine effect of macronutrient manipulation on body composition and cardiovascular risk markers in adolescents presenting for weight management. It is designed as a treatment protocol integrating psychological support with dietary change. It incorporates group based activity, individual face to face counselling and telephone support in assisting adolescents and their families with weight management.

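### The only analysis stated for metabolic markers relates them to weight and fat loss, which does not estimate the between-diet difference posed in the 12-week hypothesis

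*Protocol article*

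**What the plan says.** Under Hypotheses to be tested, After 12 weeks, the protocol article states: "There will be a difference in the change of % body fat, markers of inflammation, insulin resistance and in lipid profile", and fixes the contrast as "between the reduced carbohydrate group and the low fat group". The Methods/Design text below Figure 1 gives these outcomes their rank: "Secondary outcome variables are reduction in body fat and alteration in metabolic profile after 12 weeks".

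The Statistical Analysis Plan section says of the markers: "We will examine the effects of losses of body weight and body fat on clinically important markers of disease risk". The list and method that follow are "lipids, blood pressure, waist: hip ratio, insulin resistance) using analysis of covariance". The longitudinal model in the same section concerns weight: "We shall examine weight loss over time using a mixed-effects model with a random intercept and slope for each participant". A further set of mixed-effects models is for the psychometric questionnaires. Tests are two-sided at the 5% level.

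The Discussion adds a remark on practice: "If the reduction in dietary carbohydrate has no adverse effects on cardiovascular risk factors, the option to decrease carbohydrate would broaden the choice".

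**The concern.** The hypothesis is about randomised diets. The stated marker analysis is about how much weight or fat a participant lost, which is known only after randomisation and may itself be a result of the diet. Participants who lose more weight differ from those who lose less in adherence, family support, puberty and much else, so the comparison is not protected by randomisation.

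The outcomes do not match either. The hypothesis names body fat percentage and inflammatory markers. In the stated analysis, body fat is an explanatory variable only, and inflammatory markers do not appear, although the section Adipokines and inflammatory markers has them measured at M1 and M2.

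At stake is the trial's cardiometabolic question. An analyst who followed the text as written could report a firm result on weight loss and markers without ever estimating what the choice of diet did to them.

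**Working it through.** **1. Question and analysis side by side**

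| | 12-week hypothesis | Stated marker analysis |
|---|---|---|
| Explanatory variable | Randomised diet | Loss of weight and of body fat |
| Body fat | Outcome | Explanatory variable |
| Inflammatory markers | Outcome | Absent |
| Insulin resistance, lipids | Outcomes | Outcomes |
| Blood pressure, waist:hip ratio | Not named | Outcomes |

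No other section supplies the comparison. The mention of change across groups under Compliance and retention strategies concerns urea and urates as compliance markers.

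**2. The plan's own sample size**

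The Sample size section gives a difference of 0.09 in BMI z-score change, SD 0.12, two-sided 5% and 80% power, leading to 29 completers per diet arm. The normal approximation gives 28; the t-based calculation gives 29 (power 0.801). The figure reproduces, and 29 per arm is used below. The planned difference is 0.09/0.12 = 0.75 SD. The article gives no figure for the metabolic outcomes.

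**3. Set-up for the two possible readings**

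Write the marker as b × loss + d × diet + error. Loss is in SD units, the error SD is 1, and the diets differ in mean loss by Δ. The total diet effect, which is what the hypothesis asks for, is d + b × Δ. Each setting was simulated 4,000 times with 29 per arm. The values of b and d are assumptions; Δ is 0 or the planned 0.75.

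**4. Reading one: loss is the only explanatory variable**

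- Identical diets, marker tracks loss (b = 0.5, d = 0, Δ = 0): the loss test was significant in 95% of trials and the diet comparison in 5%.
- A true diet effect unrelated to loss (b = 0, d = 0.8, Δ = 0): the loss test was significant in 6% and the diet comparison in 84%.

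The two analyses answer different questions.

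**5. Reading two: diet arm is added beside loss**

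The arm coefficient then estimates d, not d + b × Δ.

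- b = 0.5, Δ = 0.75, d = -0.375: the total effect is -0.375 + 0.5 × 0.75 = 0. The mean adjusted estimate was -0.38 SD, significant in 26% of trials.
- b = 0.5, Δ = 0.75, d = 0: the total effect is 0.5 × 0.75 = 0.375 SD, all of it through loss. The mean adjusted estimate was about 0; the unadjusted diet comparison averaged 0.37.

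The gap b × Δ disappears only if the diets produce the same mean loss or the marker does not depend on loss. The trial is sized on the expectation that the diets differ in BMI z-score change.

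**6. Precision of the direct diet comparison**

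This does not measure the fault; it shows what the replacement analysis can deliver. Without baseline adjustment, the 95% CI half-width is t(0.975, 56) × √(2/29) = 0.53 SD, and power is 80% for a difference of about 0.75 SD. With an assumed baseline correlation of 0.7, the half-width falls to 0.526 × √(1 - 0.49) = 0.38 SD.

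**The case against.** The article never says that the analysis of covariance is the test of the 12-week metabolic hypothesis. Its marker list differs from the hypothesis in both directions, which suggests a separate explanatory question, and the Discussion does name an interest in what weight loss does to body compartments. The section is condensed throughout and names diet arm in no model, not even for the primary BMI z-score comparison. A fuller analysis plan may contain the diet comparison, and an article commonly leaves such detail to it.

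Much of this stands. A reader might infer that the investigators chose to relate markers to weight loss instead of comparing the diets. The documents do not support that: the contrast is fixed in the hypothesis, and a missing arm term in so short a text is not a decision against one. The weight-loss analysis is also legitimate as an addition.

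A reader might also infer a planned conclusion of no harm from non-significant tests, and so demand a non-inferiority margin. The documents do not support that either. The Discussion sentence is conditional, the hypotheses are of difference, and no non-inferiority claim is made.

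What the objection does not remove is that the section is not silent on these markers. It names a method, an explanatory variable and a set of outcomes, and none of these combinations estimates the difference between the diets.

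**Conclusion.** The point holds as a mismatch between a stated hypothesis and the only analysis stated for metabolic markers. As written, that analysis does not estimate the diet effect, and adding diet arm beside weight or fat loss would not give the total diet effect. Two of the four groups of outcomes in the hypothesis, body fat percentage and inflammatory markers, have no stated analysis as outcomes.

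The possible error under the adjusted reading is b × Δ. It is 0.375 SD with an assumed slope of 0.5 and the planned 0.75 SD separation, and larger or smaller for other values. The simulated percentages rest on those assumed effects and illustrate the mechanism; they do not forecast this trial's results.

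The consequence is limited to secondary outcomes. The sample size and the primary BMI z-score comparison are not affected.

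**What to change.** For each outcome in the 12-week hypothesis (body fat percentage, each inflammatory marker, insulin resistance and each lipid fraction), state as the analysis an analysis of covariance of the week-12 value on randomised diet. Adjust for that outcome's own baseline value and for gender and Tanner stage, the factors used under Allocation to groups. Do not include weight or fat loss as a covariate. Report the difference between diets with a 95% CI. With the baseline value in the model, the diet difference is the same whether the response is the week-12 value or the change, so this tests the hypothesis as worded.

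Keep the weight-loss and fat-loss analysis of covariance, labelled exploratory. If the full analysis plan already holds the diet comparison, bring the two texts into line.

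No margin is needed. A non-significant marker difference should be reported with its interval and not read as absence of harm.

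The cost is a few sentences. No new data, visits or participants are required.

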## Discussion

There is a lack of clinical studies which assess the effectiveness of specific treatment pathways for obese adolescents. In particular there is no information as to the effect of how alteration of the carbohydrate content of the diet will change body composition or metabolic parameters. This study protocol will contribute also to our understanding of body composition of obese adolescents and the effect of weight loss on different body compartment changes.

Our feasibility study suggested that tailored energy prescription and structured advice was the preferred option for treatment seeking adolescents and their families. In particular the need for information on how much to eat i.e. portion size was requested. If the reduction in dietary carbohydrate has no adverse effects on cardiovascular risk factors, the option to decrease carbohydrate would broaden the choice of dietary patterns based on preference of the adolescent and their family that could be offered in practice.

This study has a unique preparatory psychological preparatory phase and screening for psychological disturbance prior to randomisation which ensures that all subjects enter the study without any clinical levels of psychological diagnosis. The additional measurement of eating behaviours and other psychological parameters is designed to monitor any risk to psychological health associated with the intervention. The relatively short time frame allows biochemical parameters and psychological parameters to be measured before taking the study into a longer duration.

This study is designed to address the gap in the evidence base for optimal weight management interventions in obese adolescents in a clinical setting and to examine effect of macronutrient manipulation on body composition and cardiovascular risk markers in adolescents presenting for weight management. It is designed as a treatment protocol integrating psychological support with dietary change. It incorporates group based activity, individual face to face counselling and telephone support in assisting adolescents and their families with weight management.
